### Primary outcome measures

#### Meaning

The Dutch Personal Meaning Profile (PMP) is a 39-item self assessment scale for measuring meaning in life and comprises 5 subscales: religion, dedication to life, fairness of life, goal-orientedness, relationships [25].

The Dutch Post Traumatic Growth Inventory (PTGI) is a 21 item self assessment scale for measuring posttraumatic growth and comprises 5 scales: relationships, viewing new possibilities, personal strength, spirituality, appreciation of life [26].

The Ryff’s Scale of Psychological Well-being (SPWB) is a 49 item questionnaire to assess a person’s level of positive functioning and well-being and comprises 6 scales: autonomy, environmental mastery, personal growth, positive relationships, purpose in life, self-acceptance [27].

### Secondary outcome measures

#### Quality of life

The 30-item EORTC QLQ-C30 (version 3.0) includes a global HRQOL scale (2 items) and comprises 5 functional scales: physical functioning (5 items), role functioning (2 items), emotional functioning (4 items), cognitive functioning (2 items) and social functioning (2 items). There are three symptom scales (nausea and vomiting (2 items), fatigue (3 items) and pain (2 items) and 6 single items relating to dyspnoea, insomnia, loss of appetite, constipation, diarrhoea and financial difficulties [28,29].

### Anxiety and depression

A validated Dutch version of the Hospital Anxiety and Depression Scale (HADS) is used to assess emotional distress. The HADS is a 14-item self-assessment scale for measuring distress with two subscales, anxiety and depression. The HADS was specifically designed for use in the medically ill. The total HADS score ranges from 0 to 42, the subscales from 0 to 21. A score of >15 is used as an indicator of a high level of psychological distress [30].

### Hopelessness

The Dutch Beck Hopelessness Scale (BHS) is a 20 item self-assessment scale for measuring hopelessness. The scale consists of 20 statements about oneself which are endorsed as true or false. The content of 11 statements is hopeless, the content of 9 statements is hopeful [31,32].

### Optimism

The Dutch Life Orientation Test (LOT-R), is a 10-item self-assessment scale for measuring optimism. The scale consists of 10 statements about oneself which are endorsed on a 5-point likert scale (from 1 totally disagree to 5 totally agree) [33,34].

### Adjustment to cancer

Cognitive and behavioural response to cancer diagnosis and treatment is determined by the Mental Adjustment to Cancer (MAC) questionnaire. The MAC scale comprises five subscales: Fighting Spirit, Helplessness/Hopelessness, Anxious Preoccupation, Fatalism and Avoidance [20].

### Satisfaction with the intervention

At T1, cancer survivors in both the MCGP-CS and SGP study arms are asked to evaluate the strengths and weaknesses of the group training that they received and rate their satisfaction with the content, duration, and quality of the training and the trainers on a 15 item likert-scaled questionnaire and on free text responses. Participants in the MCGP-CS condition are asked three additional evaluation questions about the specific content of the MCGP-CS protocol (their opinion on talking about meaning, the homework assignments and the workbook).

### Cost-evaluation

Direct medical and direct non-medical cost data are collected with the Trimbos and iMTA questionnaire on Costs associated with Psychiatric illness (TiC-P) [35,36]. Unit resource use (GP visits, hospital days, etc.) will be multiplied by their appropriate integral cost prices.

An economic evaluation regarding work (loss) and health care use will be conducted as a cost-utility analysis for (changes in) health-related quality of life as assessed with the EQ-5D [37].

Indirect non-medical cost data related to production losses through work loss days and work cutback days will be sampled with the appropriate PRODISQ modules [38]. Indicators of return to work (RTW) are: Time to partial and to full RTW, meaning number of calendar days between end of treatment and first day at work; Time to full RTW corrected for partial RTW.

### Sample size

Based on a priori power analyses for hierarchical multiple regression, assuming a power of .80, Cohen’s d of .80 and alpha of .05, each study condition will need at least 43 cancer survivors. We will anticipate for loss to follow-up of 30%, and will therefore need 56 cancer survivors per condition at baseline. In total, we will recruit 168 cancer survivors during an inclusion period of 2.5 years.

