## Methods/Design

### Design

This study is a prospective randomized controlled trial with three study arms: MCGP-CS, SGP and CAU. Cancer survivors are recruited in two different ways: via several hospitals in the Netherlands (region Leiden and Amsterdam) and via public media (i.e. advertisement on websites of patient societies, and in magazines and local newspapers). All cancer survivors who meet in- and exclusion criteria are asked to participate. Survivors are assigned through cluster randomisation to one of the three study arms. The baseline assessment takes place before randomisation, with follow up assessments one week post-intervention and at 3, 6 and 12 months follow-up. Reasons for dropout are registered. The study protocol, information brochure, questionnaires and informed consent form are approved as a multicenter study by the Medical Ethics Committee of the Leiden University Medical Center. The design is illustrated in Figure 1.

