### Statistical analyses

Descriptive statistics, t-tests and Chi^2^ tests will be used to determine whether patient characteristics are similar across experimental conditions. Results will be reported on an intention-to-treat basis. The Linear Mixed Modeling (LMM) procedure will be used to estimate missing values. This procedure includes incomplete cases in the analysis and employs restricted maximum likelihood estimation to calculate parameter estimates. LMM assumes that missing data are missing at random. LMM will be used to investigate the longitudinal development of meaning making in the three groups. The effect of study condition will be tested using contrasts within the LMM. Mediation analyses [39,40] will be used to test as whether development in the patients’ meaning making explains/mediates the expected improvement in psychological functioning in the MCGP condition.

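### The 43 per condition does not follow from the stated inputs, and no basis is given for 80% power in a trial that randomises groups of 8 and tests LMM contrasts

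*Protocol article*

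**What the plan says.** The Sample size section of the protocol article rests on "a priori power analyses for hierarchical multiple regression, assuming a power of .80". Its other inputs are Cohen's "d of .80 and alpha of .05". It concludes that "each study condition will need at least 43 cancer survivors", raises this to 56 for an expected 30% loss, and arrives at 168 in total. It does not give the sidedness, the number of predictors, the contrast, an ICC or a design effect.

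The Design section says: "Survivors are assigned through cluster randomisation to one of the three study arms". The Randomization section fixes the unit: a group is allocated once it holds 8 survivors. The Statistical analyses section says: "The effect of study condition will be tested using contrasts within the LMM".

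**The concern.** Cohen's d is a two-group standardised difference. With d = 0.80, power 0.80 and alpha 0.05, the familiar answer is in the mid-twenties per arm, so 43 looks too large for its own inputs. The paragraph also names a model the trial will not use for its main comparison, and it is silent on clustering although whole groups are randomised.

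This paragraph is the article's only justification for 168. If its figure cannot be reproduced and refers to a different model and unit, a reader cannot tell what power the trial has for d = 0.80, or what difference it can detect.

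**Working it through.** **Inputs from the protocol article.** Power 0.80, d = 0.80, alpha 0.05, 43 analysed and 56 recruited per arm, 30% loss, 168 in total (Sample size); groups of 8 (Randomization); three arms (Design). Two-sided testing and every ICC below are assumptions.

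**1. Attempt to reproduce 43.** Normal approximation: n per arm = 2(1.960 + 0.842)² / 0.80² = 24.5, so 25. Exact noncentral t: 25 per arm gives power 0.791 and 26 gives 0.807, so 26 are needed. At 43 per arm the power is 0.956; equivalently, 43 per arm has 80% power for d of about 0.61.

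**2. Variants.** None of these gives 43 per arm from the stated inputs:

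| Variant | Result |
|---|---|
| One-sided t test | 21 per arm |
| Two-sided, alpha 0.05/3 | 35 per arm |
| Three-arm ANOVA | 24 to 32 per arm |
| Regression F test, f² = d²/4 = 0.16, 1 to 7 predictors | total N 52 to 97 |

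A figure of 42 or 43 appears only with something the article does not state:

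| Unstated input | Result |
|---|---|
| Power 0.95 | 42 per arm |
| Alpha 0.05/9 | 43 per arm |
| f² = 0.35 with 5 predictors | total N 43, not per arm |
| ICC 0.10 in groups of 8: 25 × (1 + 7 × 0.10) = 25 × 1.7 | 42.5, so 43 per arm |
| Three-arm conversion of d, 5 tested predictors | total N 126 to 136 (42 to 45 per arm) |

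Several routes lead to the same figure, so its origin cannot be determined from the document.

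**3. Design against calculation.** 168 / 8 = 21 groups, 7 per arm. The calculation names a regression; the test is an LMM contrast; the randomised unit is the group. Nothing in the article links these.

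**4. Loss to follow-up.** 43 × 1.3 = 55.9, which reproduces the 56. But 56 × 0.7 = 39.2, so about 39 per arm remain, below the plan's own minimum of 43. Retaining 43 after 30% loss would need 43 / 0.7 = 61.4, so 62.

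**5. Illustrative power for the trial as designed.** 7 groups per arm and 39.2 evaluable per arm give 39.2 / 7 = 5.6 per group. Design effect DE = 1 + (5.6 − 1) × ICC. Standard error of the standardised difference = √(2 × DE / 39.2). Noncentral t with 12 df (two arms, 2 × 6) or 18 df (three arms, 3 × 6), two-sided alpha 0.05, one post-baseline contrast, no baseline adjustment.

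| ICC (assumed) | DE | SE | Power at d = 0.80 (12 to 18 df) |
|---|---|---|---|
| 0 | 1.00 | 0.226 | 0.90-0.92 |
| 0.05 | 1.23 | 0.251 | 0.83-0.86 |
| 0.10 | 1.46 | 0.273 | 0.77-0.79 |
| 0.15 | 1.69 | 0.294 | 0.71-0.73 |

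The detectable d at 80% power is 0.67-0.69 at ICC 0 and 0.81-0.83 at ICC 0.10.

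**The case against.** The best defence is that the article is silent on clustering rather than wrong about it. An undisclosed ICC of 0.10 with groups of 8 gives 43, so an allowance may have been made. That stands as a limit on what can be said about origin. A reader might infer that 43 came from a calculation for independent observations, or that a whole-model regression total was used per arm by mistake. The regression wording makes independence the usual reading, but the text settles neither. If a design effect was used, it is undisclosed and the stated regression basis misdescribes the calculation, so the paragraph still needs the same correction.

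A second tempting reading is that the trial is underpowered, or that the 80% is false. The figures do not support this. With independent observations the discrepancy runs in the safe direction, and power for d = 0.80 exceeds 80% at ICC 0.05 and falls at most about 3 points short at 0.10. The illustration also leaves out features that help. An assumed baseline correlation of 0.5 multiplies the SE by √(1 − 0.25) and gives 0.87-0.89 at ICC 0.10. Care as usual involves no group sessions, so less clustering may arise in that arm. Multiplicity over three primary scales and several contrasts would pull the other way.

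Nor does it follow that a null result for MCGP-CS against SGP would be uninterpretable; that is read from the estimate and its confidence interval.

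Finally, an article may leave predictor counts and the ICC to a fuller document. That is fair for details. It does not excuse a printed figure that disagrees with its printed inputs, or a named model that differs from the planned analysis.

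**Conclusion.** Wrong as written. On the stated inputs the requirement is 26 per arm, not 43, and 43 per arm would give 0.956 rather than 0.80. This part assumes only a two-sided comparison of two arms, and the variants tried do not rescue the figure. The named method matches neither the LMM contrasts nor the randomisation of groups, so 80% power is not established for this design. That is different from showing that it is not met: under the assumed ICCs, power at d = 0.80 runs from about 0.92 down to 0.71 as the ICC goes from 0 to 0.15. These values rest on equal group sizes after loss and the same ICC in every arm.

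**What to change.** Keep 168. Remove the regression basis and replace the paragraph with a calculation for the arm contrast that will be tested. It should state:

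- the contrast and time point, the sidedness, and the alpha of the primary contrast;
- 7 groups of 8 per arm, and about 39 evaluable per arm after 30% loss, noting that this is below the stated minimum of 43;
- an ICC range of 0 to 0.10 or wider, with the design effect and group-based degrees of freedom;
- any credit taken for baseline adjustment or repeated measures, with the assumed correlation;
- the resulting power at d = 0.80 and the detectable d at 80% power.

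If 43 did include a clustering allowance, say so and give the ICC. The cost is one rewritten paragraph and a stated power that may be slightly less favourable. No extra participants are needed.

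### The baseline size of 56 per arm does not cover the planned 30% loss: it leaves about 39 per arm, below the stated minimum of 43

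*Protocol article*

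**What the plan says.** All the figures stand together in the Sample size section of the protocol article.

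- Basis of the calculation: "Based on a priori power analyses for hierarchical multiple regression", "assuming a power of .80, Cohen’s d of .80 and alpha of .05".
- Resulting minimum: "each study condition will need at least 43 cancer survivors".
- Allowance for loss: "We will anticipate for loss to follow-up of 30%, and will therefore need 56 cancer survivors per condition at baseline".
- Total: "In total, we will recruit 168 cancer survivors during an inclusion period of 2.5 years". This is 3 × 56, matching the three arms in the Design section.

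No other part of the article gives a different loss rate or another reason for 56.

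**The concern.** The section presents 56 as the consequence of needing 43 and expecting 30% loss. An allowance for loss has to work on the number recruited: if 30% of those recruited are lost, 70% remain, and that 70% must be at least 43. Adding 30% of 43 to 43 does something else, and always gives too few.

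What is at stake is a stated property of the design. Readers, funders and the ethics committee are told that 168 survivors protect the planned power against 30% loss. If that is not so, the trial can fall below its own minimum while loss runs exactly as expected. The background section criticises earlier studies for high dropout, so the margin for loss should be stated correctly.

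**Working it through.** **Inputs (all from the Sample size section)**

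- Minimum per arm after loss: n = 43
- Expected loss: L = 0.30
- Stated baseline number per arm: 56, with 168 in total
- Power 0.80, Cohen's d 0.80, alpha 0.05 (sidedness not stated; two-sided assumed below)

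**Step 1. Reproduce the plan's figure.**
n × (1 + L) = 43 × 1.30 = 55.9, rounded up to 56. This matches exactly.

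**Step 2. Apply the loss to the baseline number.**
n / (1 − L) = 43 / 0.70 = 61.4, rounded up to 62 per arm. In total 3 × 62 = 186, which is 18 more than 168.

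**Step 3. See what 56 leaves.**
56 × (1 − 0.30) = 39.2, about 39 per arm. The shortfall is 43 − 39 = 4 per arm (4/43 = 9%), about 12 over three arms.

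**Step 4. Find the loss that 56 does cover.**
1 − 43/56 = 0.232. So 56 keeps 43 only up to 23.2% loss. At 25% loss, 42 remain.

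**Step 5. Size the effect on power.** The plan's method cannot be rebuilt in full because the number of predictors is not given, so three readings are shown. All ignore clustering.

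| Reading | 43 per arm | 39 per arm |
|---|---|---|
| Power, if 43 gives exactly 80% (normal approximation) | 80% | 76% |
| Power, regression F-test with f² = d²/4 = 0.16, 5 predictors (assumed), two arms (N = 86 and N = 78) | 80.1% | 75.1% |
| Effect detectable with 80% power, plain two-sample t-test | d = 0.61 | d = 0.64 |

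The first row scales the noncentrality with the square root of n: (1.960 + 0.842) × √(39/43) − 1.960 = 0.708, and Φ(0.708) = 0.76. In the second row, the assumption of five predictors gives N = 86 for two arms, or 43 per arm. That makes it a plausible reading of the plan's method, but it remains an assumption. Steps 1 to 4 do not depend on it.

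**The case against.** Nobody can dispute the arithmetic. The best case on the other side is that it hardly matters.

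- **The analysis keeps incomplete cases.** The Statistical analyses section specifies intention-to-treat with a linear mixed model that uses participants with missing assessments, and the primary outcomes are measured at five time points. Someone lost after the post-intervention assessment still contributes. So 39 counts completers, not people analysed, and the information lost may be less than 30%. This stands and softens the consequence. It does not repair the sample size section, which itself applies the 30% to a required 43 and makes no use of partial data.

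- **Power looks ample.** A plain two-sample t-test at d = 0.80 needs about 26 per arm, and with 39 its power is about 94% (96% with 43). This also limits the practical harm. But the plan set 43, not 26, as its minimum under its own method. The 94% also treats participants as independent, whereas the Randomization section assigns whole groups of 8, and the Sample size section mentions no allowance for that. The article gives no intraclass correlation. As an illustration only, assumed values of 0.02 to 0.10 give design effects of 1 + 7 × 0.02 = 1.14 to 1 + 7 × 0.10 = 1.70, which cut 39 to an effective 34 to 23. The apparent surplus cannot simply be taken to absorb the shortfall.

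- **56 is seven groups of 8.** True, and it fits the group size. The section does not give this as the reason, and it would not make 43 survive a 30% loss.

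- **The mechanism is inferred.** The article shows no formula, so multiplication by 1.3 is an inference from an exact match. The firm claim is that 56 less 30% is below 43, and that needs no inference.

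**Conclusion.** The concern holds. On the plan's own three numbers, 56 per arm does not retain 43 after 30% loss. It retains about 39, a shortfall of about 4 per arm, and it covers a loss of only 23.2%. Full cover would take 62 per arm, or 186 in total.

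The consequence is modest: a loss of about 4 to 5 percentage points of power if 43 is the true requirement, and less if partly observed participants contribute much to the mixed model. The power figures rest on two-sided testing, no clustering and, for the regression reading, an assumed five predictors. The shortfall itself rests on nothing beyond the figures in the section. It must be corrected because a stated property of the sample size is untrue as written, not because the trial is badly underpowered by this alone.

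**What to change.** Keep 168 and correct the sentence, in one of two ways:

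1. State that 56 per arm retains the required 43 provided loss does not exceed about 23%.
2. Keep the 30% expectation, state that about 39 per arm would then complete follow-up, and restate the power or the detectable effect for 39 under the method actually used.

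Either sentence should be worded as conditional on the figure of 43, whose derivation cannot be checked from the article. If the sponsor wants to rely on the mixed model's use of partial data to close the gap, the section should say so. In no version should 56 be presented as covering a 30% loss.

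The cost is one sentence that reads slightly less favourably. No participants are added and the design does not change.

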### Statistical analyses

Descriptive statistics, t-tests and Chi^2^ tests will be used to determine whether patient characteristics are similar across experimental conditions. Results will be reported on an intention-to-treat basis. The Linear Mixed Modeling (LMM) procedure will be used to estimate missing values. This procedure includes incomplete cases in the analysis and employs restricted maximum likelihood estimation to calculate parameter estimates. LMM assumes that missing data are missing at random. LMM will be used to investigate the longitudinal development of meaning making in the three groups. The effect of study condition will be tested using contrasts within the LMM. Mediation analyses [39,40] will be used to test as whether development in the patients’ meaning making explains/mediates the expected improvement in psychological functioning in the MCGP condition.

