### Randomization

Cancer survivors who meet the inclusion criteria and sign the informed consent, are allocated to a group. When the group counts 8 survivors, the group is randomly assigned by an independent researcher, through blocked randomization with randomly selected block sizes, to one of the three study arms.

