### Economic outcomes

For the economic evaluation we will make use of the pertinent guidelines [36,41-43]. The societal perspective will be taken encompassing intervention costs, direct non-medical costs and indirect costs. The latter is not expected to be very important in the studied population, which is characterised by unemployment, but the data on production losses will be collected anyway. Production losses will be economically valuated using the friction cost method [44]. Costs and effects will be analysed simultaneously, incremental cost-effectiveness ratios (ICERs) will be calculated and placed within 95% confidence intervals, 2,500 bootstrap replications of the ICERs will be projected on a cost-effectiveness plane, ICER acceptability curves will be plotted against different willingness-to-pay ceilings [45], and sensitivity analysis will be conducted as a matter of course focussing on uncertainty in the main cost-drivers. This will be done for the costs per QALY gained in a cost utility analysis.

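### Whole groups of 8 are randomised, but neither the LMM contrasts nor the sample size carries a therapy-group level; without one, the 5% level is exceeded for any positive within-group correlation

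*Protocol article*

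**What the plan says.** The Design section of the protocol article states: "Survivors are assigned through cluster randomisation to one of the three study arms". The Randomization section gives the mechanism: "When the group counts 8 survivors, the group is randomly assigned by an independent researcher". The randomised unit is therefore the group.

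The Statistical analyses section gives the LMM two tasks, handling incomplete data and following change over time: "LMM will be used to investigate the longitudinal development of meaning making in the three groups". The effect of study condition is then tested by contrasts within that model. The section names the estimator (restricted maximum likelihood) and the missing-data assumption (missing at random). It does not mention the therapy group.

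The Sample size section works in individuals throughout: "assuming a power of .80, Cohen’s d of .80 and alpha of .05, each study condition will need at least 43 cancer survivors", then "will therefore need 56 cancer survivors per condition at baseline". It gives no ICC, design effect or number of groups.

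**The concern.** Members of one randomised group may have correlated outcomes. In the MCGP-CS and SGP arms they also share eight weekly two-hour sessions and a psychotherapist. A random effect for the participant captures correlation between one person's repeated measurements, but not correlation between people in the same group. A contrast fitted without a group level treats the 56 people in an arm as independent, when the arm consists of 7 randomised units.

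At stake is the claim of effectiveness. Standard errors that are too small give intervals that are too narrow and make a false positive more likely. MCGP-CS v SGP is the most exposed comparison, because both arms meet as groups. It is also the comparison that isolates the meaning-centred content, and the Discussion ties a positive result to implementation in care.

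**Working it through.** **Inputs from the article.** Groups of 8 (Randomization). 43 evaluable and 56 recruited per condition, 168 in total, 30% loss (Sample size). Alpha 0.05 is stated without sidedness; two-sided is taken. No ICC is given, so 0.02 to 0.10 is assumed as the main range.

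**The plan's own figures.** 43 × 1.3 = 55.9, which gives the stated 56, and 3 × 56 = 168. Hence 168/8 = 21 groups and 56/8 = 7 per arm. The 43 does not follow from d = 0.80, power 0.80 and alpha 0.05 in a plain two-arm comparison (25 to 26 per arm). The inputs to the regression calculation are not stated. That is a separate matter, but nothing stated shows that the 43 contains an allowance for clustering.

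**Group size after loss.** 56 × 0.7 = 39.2 per arm, and 39.2/7 = 5.6 per group.

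**Formulas**, with m people per group:
- Design effect: DE = 1 + (m − 1) × ICC
- Share by which the standard error is understated if groups are ignored: 1 − 1/√DE
- True size of a nominal two-sided 5% test: 2 × (1 − Φ(1.96/√DE))

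**Both arms clustered (MCGP-CS v SGP)**

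| m | ICC | DE | √DE | SE understated | True error |
|---|---|---|---|---|---|
| 8 | 0.02 | 1.14 | 1.068 | 6% | 6.6% |
| 8 | 0.05 | 1.35 | 1.162 | 14% | 9.2% |
| 8 | 0.10 | 1.70 | 1.304 | 23% | 13.3% |
| 5.6 | 0.02 | 1.092 | 1.045 | 4% | 6.1% |
| 5.6 | 0.05 | 1.23 | 1.109 | 10% | 7.7% |
| 5.6 | 0.10 | 1.46 | 1.208 | 17% | 10.5% |

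Outside the main range with m = 8, the error is 5.0% at ICC 0, 5.8% at 0.01 and 20.6% at 0.20.

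**One arm clustered (either intervention v CAU, if CAU outcomes are uncorrelated).** The variance of the difference is inflated by (DE + 1)/2. With m = 8 this is 1.175 at ICC 0.05 and 1.35 at 0.10, so the true error is 7.1% and 9.2%. Simulation gave 6.7% and 9.0%, so about 7% and 9%.

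**Check by simulation** (20,000 trials, 7 v 7 groups of 8). Ignoring groups gave 5.9%, 9.1%, 13.6% and 20.9% at ICC 0.01, 0.05, 0.10 and 0.20. A t-test on the group means stayed between 4.8% and 5.2%.

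**Degrees of freedom.** With the group variance pooled over three arms, 21 − 3 = 18. If CAU has its own group variance, MCGP-CS v SGP rests on 14 groups, and 14 − 2 = 12.

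**Power of a test that respects the groups.** With 43 evaluable per arm in 7 groups, d = 0.80 and 12 df, power is 91%, 86%, 79% and 67% at ICC 0.01, 0.05, 0.10 and 0.20.

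**The case against.** The strongest objection is that this is an argument from silence. The article states no random-effects structure at all, not even at participant level. An LMM can hold a random effect for group, and nothing in the text excludes one. A reader might infer that the plan specifies an individual-level analysis, or that the 5% level is certainly lost. The documents support neither. Inflation needs both an omitted group term and a positive ICC, and no ICC is given; at 0.01 the error is only 5.8%.

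A second objection is that a condensed article normally leaves the degrees-of-freedom method, ICC reporting and the bootstrap's resampling unit to an analysis plan. That stands. The economic section's "2,500 bootstrap replications of the ICERs" names no resampling unit, and this is not counted here as a defect.

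A third is that the larger error figures do not apply to every comparison. This also stands: CAU participants attend no group intervention, so contrasts with CAU may be affected less.

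What the objections do not remove is the mismatch inside the article. It calls the design cluster randomised, goes into enough detail to name the estimator, the missing-data assumption and the form of test, and still leaves out the randomised unit. The sample size independently omits it too. The term hierarchical regression in that paragraph could be read as multilevel, but no cluster input accompanies it. Two sections that both work without the group level make this more than a detail left for later.

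**Conclusion.** The concern holds in conditional form. The design randomises 21 groups, and neither the analysis text nor the sample size carries that level. If the contrasts are run without a group term, any positive ICC takes the true error above 5%. For MCGP-CS v SGP, an ICC of 0.05 to 0.10 gives 9.2% to 13.3% with full groups, with standard errors understated by 14 to 23%. After the planned loss it gives 7.7% to 10.5%, understated by 10 to 17%. Contrasts with CAU reach about 7% to 9% with 8 per group, provided CAU outcomes are uncorrelated.

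These figures rest on an assumed ICC, equal group sizes, a two-sided test and a normal approximation that simulation supports. The number of groups is not the main difficulty: at d = 0.80 a test that respects the groups keeps 79% to 86% power over the same ICC range. What must be settled is the model, before the data are analysed.

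**What to change.** In Statistical analyses, specify an LMM with occasions nested in participants and participants nested in randomised groups. Include a random effect for group, and allow its variance to differ in CAU. Use small-sample degrees of freedom (Kenward-Roger or Satterthwaite) based on the number of groups: about 12 for MCGP-CS v SGP when the CAU variance is separate, about 18 if it is pooled. Report the estimated ICC. In Sample size, state the number of groups, the assumed ICC and the resulting design effect or power.

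As a consistent extension, resample whole groups within arm in the ICER bootstrap.

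This takes about a paragraph and no new data, since group membership is known from allocation. The price is somewhat wider intervals.
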